### Outcome measures

Schedule of enrolment, interventions, and assessments are presented in Fig 1. Baseline (T 0) data will be collected right after participants’ eligibility is determined and consent signed. Before and after completing 4 weeks intervention (T1), patients’ pre-hospital delay intentions, foot care knowledge, foot care self-efficacy, foot care behaviors, blood glucose, blood pressure, weight, and DPN syndrome, will be assessed.

**Fig 1 pone.0350892.g001:**
[figure not shown]
Schedule of enrolment, interventions, and assessments. No., number; DFU, Diabetic foot ulcer; FBG, Fasting blood glucose, PBG, post-prandial blood glucose; SBP, systolic blood pressure; DBP, diastolic blood pressure; HbA1c, glycated hemoglobin A1c.

A supplementary 3-month follow-up assessment (T2) will be conducted outside the primary RCT framework. This evaluation will replicate the baseline measurements for all outcome variables and will additionally document the incidence of DFU as a safety outcome.

### Primary outcome

#### Pre-hospital Delay Intention Survey (PHDI).

The PHDI scale, developed by Xu et al. [36], serves as a validated predictor of delay behavior in diabetic patients at risk of foot ulceration [37]. This instrument comprises seven items assessed on a 4-point Likert scale, yielding total scores between 7 and 28. Higher scores indicate stronger delay intentions. The scale demonstrates good internal consistency, with a Cronbach’s α of 0.884 [36].

### Secondary outcome

#### Audit of Diabetes Knowledge Survey (ADKnowl).

Foot-care knowledge will be assessed using the relevant dimension of the Chinese version of the ADKnowl questionnaire, which was modified and validated by Zhu [38]. This version has demonstrated strong reliability (Cronbach’s α = 0.909) and validity (content validity index = 0.923). Consistent with prior research [39], the foot-care subscale was utilized, encompassing 24 items across six domains: foot examination, daily care, toenail trimming, foot treatment, shoe selection, and skin treatment. Responses are recorded as true, false, or ‘don’t know,’ with a total possible score of 24. Higher scores indicate superior foot-care knowledge.

#### Diabetic Foot Care Self-Efficacy Scale (DSES).

Foot-care self-efficacy will be assessed using the corresponding subscale from the Chinese version of the DSES. This instrument was originally developed by Hurley and Shea [40], subsequently translated and modified by Wang [41], and validated in mainland China by Wan et al. [42], demonstrating strong reliability (Cronbach’s α = 0.91). The 5-item foot-care subscale evaluates confidence in performing key behaviors such as daily foot examination, proper footwear selection, and nail care. Items are rated on a 5-point Likert scale from “definitely not” (1 point) to “definitely yes” (5 points), yielding total scores between 5 and 25, with higher scores indicating greater self-efficacy. This focused application of the foot-care component follows established methodological precedent [39].

#### Nottingham Assessment of Functional Foot-care Questionnaire (NAFF).

Foot self-care practices will be assessed using the Chinese version of the NAFF, developed by Lincoln [43] and translated by Li et al. [44]. This 24-item instrument evaluates five behavioral domains: daily inspection, hygiene, protection, appropriate footwear, and help-seeking for foot problems. Responses are scored on a 0–3 frequency scale, with eight reverse-scored items yielding a total score range of 0–72. Higher scores indicate better self-care practices. The Chinese version demonstrates adequate reliability (Cronbach’s α = 0.77, test-retest reliability = 0.74).

#### Toronto Clinical Scoring System (TCSS).

The TCSS will be employed to assess DPN. This validated instrument combines evaluation of sensory perception, deep tendon reflexes, and neuropathic symptoms, generating a continuous score from 0 to 19 points [45]. A trained research nurse will administer the assessment using a standardized peripheral nerve testing toolkit.

### Blood glucose

Glycemic control parameters will be prospectively collected through standardized clinical procedures. Venous blood samples will be obtained after a minimum eight-hour fast to measure fasting blood glucose (FBG), postprandial blood glucose (PBG), and glycated hemoglobin (HbA1c) through biochemical analysis, with results extracted from clinical records.

### Physical examination

Physical examinations will be performed by trained research nurses using standardized procedures. Participants’ weight and height will be measured using a digital weighing scale and a stadiometer, respectively. Blood pressure measurements will record systolic (SBP) and diastolic (DBP) values using a sphygmomanometer. DFU will be also assessed.

### Statistical analyses

All statistical analyses will be performed using SPSS version 27.0 (IBM Corp., Armonk, NY, USA). Continuous variables with a normal distribution will be expressed as mean and standard deviation, while those with a non-normal distribution will be presented as median and interquartile range. Categorical variables will be summarized as frequencies and percentages and compared using the chi-square test or Fisher’s exact test as appropriate.

Longitudinal changes in primary and secondary outcomes measured at baseline, one month post-intervention, and three months post-intervention will be assessed using repeated-measures analysis of variance. The raw outcome value measured at each time point will serve as the dependent variable. Group will be treated as the between-subjects factor, and time as the within-subjects factor.

For secondary outcomes, the Bonferroni method will be applied to adjust P-values for multiple comparisons to control the type I error rate. Both intention-to-treat and per-protocol analyses will be performed. For the intention-to-treat analysis, missing data will be handled using multiple imputation under the missing at random assumption, with 20 imputed datasets generated and results pooled according to Rubin’s rules. A sensitivity analysis using complete case analysis will be conducted under the missing not at random assumption to assess the stability of the findings. Statistical significance will be defined as a two-sided adjusted P-value of less than 0.05. The study flowchart is presented in Fig 2.

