**Method:**

A multicenter randomized controlled trial will be employed. Diabetic patients at risk of foot ulceration will be recruited from two different tertiary hospitals in different cities. Eligible participants will be randomly allocated to receive either routine education and a foot-care handbook (control group) or comprehensive foot-care education based on MTM (intervention group). The intervention period will last for 4 weeks, followed by a 3-month post-intervention follow-up. Questionnaire data and clinical data will be collected at baseline, immediately after the 4-week intervention, and at the 3-month follow-up. The primary outcome will be pre-hospital delay intentions. Foot care knowledge, foot care self-efficacy, and foot care behaviors will be investigated using questionnaires. Clinical data, including blood glucose, blood pressure, and body mass index (BMI), will also be assessed.

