### Changes in the social environment

“Changes in the social environment” will be developed by tele-nursing and home visits. After discharge, the family members, friends or the primary caregivers will be invited to join in the WeChat communication group, and they could consult the doctors and nurses in the group. In addition, the researcher nurse will also provide some information regarding foot care for them via WeChat. Tele-nursing support is available throughout the 4-week intervention and follow-up. Additional home visits will be provided if required.

In order to ensure the consistent delivery of the program, we will develop a program training for research nurses. Table 1 shows the overview of the foot-care education program.

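### T2 is placed outside the primary trial yet sits in the only model for the primary outcome, and no visit or contrast is named to decide success

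*Protocol article*

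**What the plan says.** **Timing of the second assessment.** The Abstract (Method) has data collected at baseline, "immediately after the 4-week intervention, and at the 3-month follow-up". Outcome measures agrees: "Before and after completing 4 weeks intervention (T1"). Statistical analyses labels the visits differently: outcomes "measured at baseline, one month post-intervention, and three months post-intervention will be assessed using repeated-measures analysis of variance".

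**Status of T2.** In Outcome measures, after the Fig 1 legend: "A supplementary 3-month follow-up assessment (T2) will be conducted outside the primary RCT framework". In Statistical analyses, the three-month value is one of the three levels of the within-subjects factor, in the only model given for primary and secondary outcomes.

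**Primary outcome.** The Abstract states: "The primary outcome will be pre-hospital delay intentions". Neither this nor the Primary outcome section attaches a visit. Sample size calculation and allocation powers a two-sample t-test on PHDI and does not say at which visit.

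**Support after week 4.** The Abstract says: "The intervention period will last for 4 weeks, followed by a 3-month post-intervention follow-up". Changes in the social environment says: "Tele-nursing support is available throughout the 4-week intervention and follow-up". The control-group section gives controls monthly nurse calls after discharge, four in all, plus guidance from the research team.

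**The concern.** A primary analysis needs one outcome, one time and one contrast. Here only the outcome is fixed. The text gives two incompatible accounts of T2, as an add-on outside the primary trial and as part of the primary model, and two labels for T1. A repeated-measures ANOVA with group and time yields at least three candidate answers: the group main effect over all visits, the group-by-time interaction, and a between-group difference at one visit. The plan does not say which decides. Bonferroni adjustment is assigned to the secondary outcomes only, so nothing in the text restrains a choice among visits or terms for PHDI.

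Two things are at stake. The claim of success could rest on a test picked once results are known. And the test behind the sample size, a comparison of two groups at one visit, corresponds to no named term in the planned analysis.

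**Working it through.** **1. The plan's own figure.** Inputs from Sample size calculation and allocation: d = 0.80, two-sided alpha 0.05, power 0.85, two-sample t-test. With n per group, df = 2n − 2 and noncentrality d × sqrt(n/2), exact power is 0.849 at n = 29 and 0.861 at n = 30. The stated 30 per group is reproduced. It is sound for one comparison at one visit.

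**2. Candidate tests in the planned model.** The documents give neither a within-patient correlation nor a T2 effect, so these are assumptions: n = 30 per group, equal variances, compound symmetry with correlation rho, no difference at baseline, 0.80 SD at T1 and 0.40 SD at T2. The central value of rho is 0.5, with a range of 0.3 to 0.7.

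- *Group main effect, three visits.* Mean difference = (0 + 0.80 + 0.40)/3 = 0.40. SD of a patient's three-visit mean = sqrt((1 + 2 × 0.5)/3) = 0.816. Standardised effect = 0.40/0.816 = 0.49. Power 0.46.
- *Group-by-time interaction, three visits.* Deviations from the mean difference are −0.40, 0.40 and 0, with sum of squares 0.32. Noncentrality = (n/2) × 0.32/(1 − rho) = 15 × 0.32/0.5 = 9.6 on 2 and 116 df. Power 0.79.
- *t-test at one visit.* Power 0.86 if d = 0.80 there, and 0.33 if d = 0.40.

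| Test (n = 30 per group) | rho 0.3 | rho 0.5 | rho 0.7 |
|---|---|---|---|
| Group main effect, T0/T1/T2 (0, 0.80, 0.40) | 0.55 | 0.46 | 0.40 |
| Interaction, T0/T1/T2 (0, 0.80, 0.40) | 0.63 | 0.79 | 0.95 |
| Group main effect, T0/T1/T2 (0, 0.80, 0.80) | 0.79 | 0.70 | 0.62 |
| Interaction, T0/T1/T2 (0, 0.80, 0.80) | 0.77 | 0.90 | 0.99 |
| Group main effect, T0/T1 only (0, 0.80) | 0.47 | 0.42 | 0.38 |
| Interaction, T0/T1 only (0, 0.80) | 0.73 | 0.86 | 0.98 |

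**3. Where the loss comes from.** Removing T2 from the group main effect moves power from 0.46 to 0.42 at rho 0.5, so T2 is not what lowers it. Baseline, where randomisation makes the expected difference zero, is averaged in, and that is the main cause. Dropping T2 without naming a contrast would still leave 0.42 or 0.86 open, depending on which term is read.

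**4. The visit labels side by side.** The Abstract and Outcome measures agree on the end of week 4. One month post-intervention, read literally, is about week 8. Every section describes three assessments, and none schedules one at week 8.

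**The case against.** *The week-8 reading is strained.* This largely stands. The label in Statistical analyses is most likely loose wording for the assessment at the end of the 4-week programme. A reader might infer two rival T1 visits, but the text does not support that. It is a label to correct, although in the same sentence the three-month visit is also called post-intervention, and there the term does fit the Abstract's follow-up counted from the end of the programme.

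*Placing T2 outside the primary framework implies that T1 is primary.* That may be the intention, but it is not stated, and Statistical analyses contradicts it by putting T2 in the same model.

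*The power loss is not caused by T2.* Correct. A reader might infer that including T2 cuts power from 0.86 to 0.46. The working shows otherwise. The usual test of longitudinal change in such a model is the group-by-time interaction, at 0.79 under the same assumptions. But the plan does not name it.

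*Support does not continue in one arm only.* Also correct. A reader might infer that controls have nothing after week 4, but they have monthly calls and research-team guidance. What continues in the intervention arm is additional support.

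*An article may leave the contrast to a fuller plan.* It may omit detail. That does not cover conflicting statements about which data belong to the primary analysis.

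**Conclusion.** The point holds. The contradiction over T2's status is in the current text and depends on neither the missing figures nor any unseen plan. The T1 label conflicts with two other sections. No visit is attached to PHDI, and no model term is named as decisive.

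The arithmetic only illustrates how much the open choice matters. Over the tabulated scenarios and the single-visit t-tests, power runs from 0.33 to 0.99, depending on which visit and term are called primary and on assumed correlations and T2 effects. The sample size is not in error: 30 per group matches a single-visit comparison at d = 0.80.

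A lesser matter concerns interpretation at T2. Because the intervention arm's tele-nursing remains available during follow-up, a T2 difference would not show what persists once all programme support has ended.

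**What to change.** 1. In Statistical analyses, relabel the second assessment as the end of the 4-week intervention (T1), matching the Abstract and Outcome measures.
2. Name the between-group difference in PHDI at T1 as the single primary contrast, ideally adjusted for the baseline PHDI already collected. This matches the single-visit comparison in the sample-size section. Naming the visit alone is not enough, because main effect and interaction would both remain open.
3. In Outcome measures and Statistical analyses, state that T2 is a secondary comparison of the randomised groups and does not enter the primary test. The repeated-measures model can stay as a secondary analysis.
4. Reconcile the Abstract with Changes in the social environment on what continues after week 4. If the tele-nursing statement stands, report a T2 difference as an effect with additional programme support still available.

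The cost is wording in these sections and one redefined primary test, with no new data or patients. The article describes the study as pre-recruitment. The change should be made and dated before outcome data are seen, since a later choice would be open to the charge of being data-driven.

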### Sample size calculation and allocation

The sample size was calculated using G*Power 3.1 software for a two independent samples t-test. The primary outcome was pre-hospital delay intention (PHDI). A large effect size (Cohen’s d = 0.80) was adopted, which was justified by a previous study in patients with high-risk diabetic foot that reported a large effect size on pre-hospital delay intention [30]. The type I error rate (α) was set at 0.05 (two-tailed), and the statistical power (1 − β) was set at 0.85 [31]. The calculation yielded a required sample size of 30 participants per group. Accounting for an anticipated 15% attrition rate during follow-up, the final target sample size was set at 35 patients per group (total N = 70).

All the participants will be randomly divided into control group (n = 35) and intervention group (n = 35) upon admission. Randomization will be performed automatically by Microsoft Excel at enrollment. The “RAND ()” function in Microsoft Excel will be used to generate a series of random numbers by an independent researcher and kept in a sealed, opaque envelope. These numbers will be served as the basis for patient allocation into either the control group or intervention group.

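### The 85% power was calculated for a two-sample t-test and does not carry over to the planned repeated-measures ANOVA, which treats baseline as a response and includes the supplementary 3-month visit

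*Protocol article*

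**What the plan says.** The section *Sample size calculation and allocation* states: "The sample size was calculated using G*Power 3.1 software for a two independent samples t-test". PHDI is the primary outcome, the test is two-sided at 0.05, "A large effect size (Cohen’s d = 0.80) was adopted", and "the statistical power (1 − β) was set at 0.85". It concludes: "The calculation yielded a required sample size of 30 participants per group". With 15% attrition the target is 35 per group, 70 in total. The effect size is not tied to a visit.

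The section *Statistical analyses* assigns a different method to the primary and secondary outcomes: repeated-measures ANOVA over baseline and two later visits. On the response it says: "The raw outcome value measured at each time point will serve as the dependent variable". The two factors of the model are then named: "Group will be treated as the between-subjects factor, and time as the within-subjects factor". No baseline covariate appears. Bonferroni adjustment is stated for secondary outcomes only.

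The section *Outcome measures* describes the 3-month assessment (T2) as supplementary and not part of the primary randomised comparison. The analysis section nevertheless puts T2 in the same model as the primary outcome. That section dates the first follow-up one month after the intervention, whereas the abstract and *Outcome measures* place T1 at the end of the 4-week intervention. I take both to mean T1.

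**The concern.** The sample-size section and the analysis section describe different tests. A two-sample t-test compares the arms once. The stated ANOVA offers two tests of the programme, and neither is that comparison.

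- **Group-by-time interaction.** This is a 2-df test that the arm difference is the same at all three visits. It does not single out T1, and its power depends on the within-patient correlation and on what happens at T2.
- **Group main effect.** This averages the arm difference over three visits, one of which is baseline, where randomisation makes the expected difference zero. The effect is diluted, and any chance baseline imbalance enters the estimate.

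Both tests draw on T2, which the protocol itself sets apart from the primary comparison. Baseline PHDI is collected but not used as a covariate, where it would sharpen the comparison. At stake are whether 85% describes the test that will be reported, and how far the primary result depends on which term is read.

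**Working it through.** **Inputs from the protocol:** d = 0.80; two-sided α = 0.05; 30 evaluable per group; visits at baseline, T1 and T2.

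**Assumptions, because the protocol gives no figure:** within-patient correlation ρ = 0.3/0.5/0.7; compound symmetry; equal SD at each visit; d = 0.80 applies at T1; the effect at T2 either persists (0.80) or halves (0.40). Arm differences in SD units at the three visits are therefore (0, 0.8, 0.8) or (0, 0.8, 0.4).

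**1. The plan's own figure.** Two-sample t-test, noncentrality d√(n/2) = 0.80 × √15 = 3.10, 58 df: power 0.861. With 29 per group it is 0.849. So 30 per group is the smallest size that reaches 0.85, and the stated figure is reproduced.

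**2. Group-by-time interaction.** Noncentral F with df 2 and 2(2n − 2) = 116, and λ = (n/2) × Σ(m − m̄)² / (1 − ρ).

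- Persisting: m̄ = 0.533, Σ(m − m̄)² = 0.4267, λ = 6.4/(1 − ρ) = 9.14/12.8/21.3.
- Halved: m̄ = 0.40, Σ(m − m̄)² = 0.32, λ = 4.8/(1 − ρ) = 6.86/9.6/16.0.

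**3. Group main effect.** The mean difference over the three visits is 1.6/3 = 0.53 SD (persisting) or 1.2/3 = 0.40 SD (halved). The SD of a patient's three-visit mean is √((1 + 2ρ)/3) = 0.730/0.816/0.894. The standardised effect is therefore 0.73/0.65/0.60 or 0.55/0.49/0.45, entered in a noncentral t with 58 df.

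**4. Baseline-adjusted ANCOVA at T1.** Standardised effect 0.80/√(1 − ρ²) = 0.84/0.92/1.12, 57 df.

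| Test, 30 per group | ρ = 0.3 | ρ = 0.5 | ρ = 0.7 |
|---|---|---|---|
| t-test as sized | 0.861 | 0.861 | 0.861 |
| Interaction, persisting | 0.766 | 0.896 | 0.988 |
| Interaction, halved | 0.634 | 0.787 | 0.952 |
| Main effect, persisting | 0.794 | 0.701 | 0.622 |
| Main effect, halved | 0.550 | 0.463 | 0.399 |
| ANCOVA at T1 | 0.891 | 0.940 | 0.989 |

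A simulation of 6,000 trials per ρ for the persisting pattern agreed with the ANOVA rows to about one percentage point.

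**5. Where 85% is reached.** The interaction reaches it from ρ of about 0.43 (persisting) or 0.58 (halved). The main effect reaches it only for ρ up to about 0.18 (persisting), and at no ρ from zero upwards if the effect halves.

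**6. All 35 per group analysed without loss** (an upper bound, because imputation does not restore lost information). Persisting: interaction 0.832/0.938/0.996, main effect 0.854/0.768/0.691. Halved: interaction 0.707/0.851/0.976, main effect 0.617/0.524/0.454.

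**The case against.** The strongest defence is that the analysis section speaks of longitudinal change, with group and time as factors, so the interaction is the natural reading. The interaction removes any constant difference between arms, so dilution and chance baseline imbalance are faults of the main effect only. At moderate to high correlation its power exceeds 85%. The single-df comparison of change from baseline to T1 has power 0.861 at ρ = 0.5, exactly that of the t-test. All of this stands. A reader might infer that the planned ANOVA lacks 85% power; the documents do not support that, because they give no correlation and the answer turns on it.

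It is also fair that repeated-measures ANOVA with baseline as a time level is a valid randomised comparison, that forgoing ANCOVA costs efficiency and not validity, and that naming the decisive term is often left to the statistical analysis plan. The point does not rest on that omission. The protocol does state the model, the response and the visits, and these do not match its sizing test or its own status for T2.

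A reader might further infer that this ANOVA cannot be combined with the planned pooling by Rubin's rules. That is wrong: the group effect is a 1-df estimate with a standard error, and the 2-df interaction can be pooled by the multivariate form of the rules.

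**Conclusion.** The concern holds in this form: the sample size is correct for the t-test (power 0.861), but 85% is not established for the stated analysis. Over ρ from 0.3 to 0.7, and with the effect at T2 either persisting or halved, power runs from 0.63 to 0.99 for the interaction and from 0.40 to 0.79 for the group main effect. These ranges rest on 30 evaluable per group, compound symmetry, d = 0.80 placed at T1, and assumed values for the correlation and the T2 effect.

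The conflict over T2 needs no assumption. One section keeps that visit apart from the primary comparison, and another puts it in the primary model. The consequence is a loss of focus and possibly of power in the primary test. It is not an invalid comparison and not a sample that is too small.

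**What to change.** Make the single primary test the baseline-adjusted group difference in PHDI at T1, two-sided at 0.05. Use either ANCOVA of T1 PHDI on group and baseline PHDI, or a linear mixed model of T1 and T2 PHDI with group, visit, group-by-visit and baseline PHDI as a covariate, the T1 contrast being primary. Baseline then leaves the response. Terms for hospital and baseline-by-visit are optional. Report T2 as secondary, which agrees with *Outcome measures*, and use one definition of T1 throughout.

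In the sample-size section, say that d = 0.80 refers to T1 and that the t-test calculation is conservative for a baseline-adjusted test. N = 70 stays.

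The cost is a change of wording. Baseline PHDI is already collected, no patients or visits are added, and the protocol describes the study as not yet recruiting.

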### Behavioral confidence

For the “behavioral confidence” construct, health education lectures will be held by the research team who have been specifically trained. The education session will be delivered to participants with PowerPoint and video presentation for about one hour in the clinical ward, along with their family members or carers. On days 4–7 of admission, the nurses will demonstrate and instruct the patients on proper foot care. The ‘teach-back’ method will be introduced to improve the patients’ comprehension [35].

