### Emotional transformation

The intervention features a multi-sensory simulation of the DF experience, which aligns with the MTM’s “emotional transformation” framework. Participants will undergo a standardized protocol where a 2 kg sandbag is attached to their ankles to mimic symptoms of lower extremity arterial disease, and sponge platforms will be used to induce neuropathic sensory differences. This immersive activity is designed to promote emotional engagement with potential foot complications.

Post-discharge support will be sustained via a dedicated WeChat platform, including: 1) a public account for structured educational content, and 2) a communication group for peer interaction and consultation with the research team. Additional one-to-one follow-ups will provide personalized psychological support and address individual patient concerns. The specific content pushed via the WeChat public account is detailed in Table 1.

**Table 1 pone.0350892.t001:** Overview of the foot-care education program.

Module		Time	Methods	Content
**Initiation of Behavior Change**	Participatory Dialogue	Days 1–3 of admission	One-on-one face-to-face communication	1.1 Clinical manifestations and severity of diabetic foot

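### Only the intervention arm shares a WeChat peer group, yet the sample size and the primary ANOVA treat all patients as independent, so the standard error may be too small

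*Protocol article*

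**What the plan says.** Under Sample size calculation and allocation, the trial is sized on PHDI with a test for independent patients: "The sample size was calculated using G*Power 3.1 software for a two independent samples t-test". The inputs are a two-sided alpha of 0.05, power 0.85 and a standardised difference of 0.80, giving 30 per group and 35 after attrition.

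Under Statistical analyses, the model for primary and secondary outcomes is a repeated-measures ANOVA over baseline, T1 and T2: "Group will be treated as the between-subjects factor, and time as the within-subjects factor". No other factor is named.

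The intervention arm's support after discharge includes "a communication group for peer interaction and consultation with the research team" (Emotional transformation). Relatives join too: "the family members, friends or the primary caregivers will be invited to join in the WeChat communication group" (Changes in the social environment). Table 1 again lists a WeChat group under family engagement, and seeking medical help is among the topics sent to the group. The control arm receives ward education, a handbook and individual monthly telephone calls, with no peer group.

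**The concern.** This is a partially nested design: individual randomisation, with shared delivery in one arm. Peer influence is a named mechanism. The Introduction lists a supportive network among the constructs that sustain change, and the Discussion relies on social networks to maintain it. Whatever is particular to one group (an influential member, a moderator, the tone of talk about when to see a doctor) can move its members' PHDI scores together. An analysis that assumes independence counts that common movement as separate evidence from each patient.

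At stake are the stated two-sided 5% level and the width of the confidence interval for the primary outcome. With a single group, its own effect is also completely confounded with the programme effect, and no model term can separate the two.

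**Working it through.** **The plan's own figure.** With d = 0.80 and two-sided alpha 0.05, the noncentral t distribution gives power 0.849 at 29 per group and 0.861 at 30. The stated 30 per group reproduces. With 15% attrition, 35 × 0.85 = 29.75, so about 30 completers per arm are used below.

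**Inputs the article does not give (assumptions).** ICC of outcomes within a WeChat group: 0.01 to 0.10. Intervention patients per group, m: 30 (one group), 15 (one per hospital), or 5.

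**Formula.** Clustering in one arm multiplies that arm's variance by 1 + (m − 1) × ICC. With equal arms, the true standard error is the assumed one times

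k = √[(1 + 1 + (m − 1) × ICC) / 2],

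and the actual level of a nominal 5% test is 2 × [1 − Φ(1.96 / k)].

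Example, one group and ICC 0.05: 1 + 29 × 0.05 = 2.45; k = √(3.45 / 2) = 1.313; 1.96 / 1.313 = 1.49; level 13.6%.

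| ICC | m = 30 | m = 15 | m = 5 |
|---|---|---|---|
| 0.01 | 6.7% | 5.8% | 5.2% |
| 0.02 | 8.4% | 6.6% | 5.5% |
| 0.05 | 13.6% | 9.2% | 6.2% |
| 0.10 | 21.1% | 13.3% | 7.4% |

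**Simulation of the planned ANOVA.** 20,000 trials per setting, 30 per arm, three visits with correlation 0.5, and a shared effect in the intervention arm at T1 and T2 only. The group-by-time test rejects in 4.8% of trials at ICC 0. With one group it rejects in 6.8%, 8.3%, 13.5% and 21.5% at ICC 0.01, 0.02, 0.05 and 0.10; with two groups, in 6.0%, 6.2%, 8.8% and 13.1%. The group main effect with one group gives 6.2%, 7.1%, 10.7% and 17.1%; it is lower because baseline dilutes it. The conclusion therefore does not depend on which term is the primary test. At ICC 0.05 with one group, a visit correlation of 0.3 or 0.7 instead of 0.5 gives 10.7% or 19.0%.

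**Rolling entry.** Recruitment runs from 1 February to 31 May 2026, 17 weeks, so members do not all share the same group at the same time. Suppose entry is even and the correlation of the group effect between two patients fades as exp(−gap/τ). The average over pairs is

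c = 2x − 2x²(1 − e^(−1/x)), with x = τ/17.

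For τ = 4, 8 and 17 weeks, c = 0.36, 0.55 and 0.74. Replacing ICC by c × ICC for a comparison at T1:

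- One group, ICC 0.05: 8.1%, 9.8% and 11.3% for the three values of τ.
- One group, extremes: 6.2% (ICC 0.02, τ = 4) to 17.3% (ICC 0.10, τ = 17).
- Two groups, ICC 0.05: 6.5% to 8.1%.

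A group-by-time test that also uses T2 lies somewhat higher than these T1 figures.

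**The case against.** The case against is substantial, and much of it stands.

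- **The size rests on unstated inputs.** A reader might infer that the false-positive rate is well above 5%. The article does not support that as fact. It gives no ICC, and a single group is only the natural reading of a singular noun. The number of groups is operational detail that an article may leave to the full protocol, so its absence is no fault.
- **Strict null.** If the programme, WeChat group included, changed nobody's score, individual randomisation would keep the level near 5%. The inflated rates concern the null of no effect on average over the groups that might have formed. That is still the relevant null for a programme the abstract offers to hospitals and community services generally, but the distinction is fair.
- **Ward lectures.** A reader might add these as a second source of clustering. The article says "The education session will be delivered to participants with PowerPoint and video presentation for about one hour in the clinical ward" but not how many attend. With even accrual, 35 patients over 17 weeks in two hospitals is about one per hospital per week, and lectures fall on days 4-7 of admission. A session would typically hold one or two trial patients, so lectures are not a firm basis.
- **Individual delivery.** The dialogue, teach-back, supplies, diary and weekly contacts are individual. This argues for a small ICC, not for zero.
- **Splitting into closed groups.** A reader might conclude that small closed groups are required. At about one patient per hospital per week, a group of five takes about five weeks to fill, longer than the four-week intervention. Splitting would change what is delivered and does not follow from the concern.

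What remains is not an omission that an unseen analysis plan would cure. The sizing and the model are stated, both assume independence, and the described delivery gives a specific reason to doubt it in one arm.

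**Conclusion.** The concern holds in a conditional form. Shared delivery in one arm and an analysis assuming independence are both in the text, so the standard error for PHDI may be too small. Its size depends on an assumed ICC, the number of groups and how long a shared effect lasts.

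With 30 completers per arm and ICC 0.02 to 0.10, the level is about 8-22% for one fully shared group and about 6.5-13% for one per hospital. Rolling entry brings the one-group range to about 6-18%. At ICC 0.01 or less it is about 5-7% whatever the grouping, and with groups of about five it is 5-6% up to ICC 0.05 and just over 7% at 0.10. The article does not show which of these applies.

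**What to change.** Keep the delivery as planned and make these changes before recruitment starts:

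1. Record each intervention patient's WeChat group and date of entry.
2. In Statistical analyses, analyse post-baseline PHDI with baseline PHDI as covariate.
3. If there are several groups, add a random effect for WeChat group in the intervention arm only, each control being its own unit, with Satterthwaite or Kenward-Roger degrees of freedom.
4. If there are only one or two groups, a random effect cannot be usefully estimated. Report the primary result also with its standard error multiplied by k over a stated ICC range, for example 0.01 to 0.10. With m = 30, k runs from √(2.29/2) = 1.07 to √(4.9/2) = 1.57; with m = 15, from √(2.14/2) = 1.03 to √(3.4/2) = 1.30. State that the programme effect cannot be separated from the effect of that group or those groups.
5. In the sample size section, state the ICC assumed and the power that follows.

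The cost is one or two extra variables and a mixed-model specification that SPSS can fit. Intervals become wider. Compared like for like, in a simulation with groups of five, ICC 0.05 and visit correlation 0.5, baseline-adjusted power at d = 0.80 falls from about 92% when groups are ignored to about 86% when a test on group means respects them. The false-positive rate falls from about 6.5% to about 5.4%. Power stays at about the planned 85% because of the baseline covariate, which is already collected. That simulation used group means, not the mixed model itself, and does not carry over to one or two groups.
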